**Fig 1 pone.0305729.g001:**
[figure not shown]
SPIRIT figure; schedule of enrolment, intervention, and assessments. *During enrolment, informed consent and eligibility screening will be conducted. Group allocation will be conducted immediately after if the participant meets the screening criteria. Thereafter, baseline assessments will be conducted immediately in the same session as well.

This study will be conducted in accordance with the latest version of the Declaration of Helsinki. Ethical approval for the study protocol was obtained from the National Healthcare Group’s Domain Specific Review Board (DSRB No: 2022/00029) (see S3 and S4 Files). Participation is voluntary and withdrawal from the study is possible at any point in time. Participants may also be asked to stop their participation at any time if they do not follow instructions required to complete the study adequately. All participants will provide written informed consent prior to their participation. Please refer to Fig 2 for the flow of the study procedure.

**Fig 2 pone.0305729.g002:**
[figure not shown]
Flow chart of study procedure.

### Intervention components

*Kampung Care* is a mobile app developed by the study team to promote the mental health of informal caregivers of PWD in Singapore. The app’s functions include a positive reflection journal, online peer support forum, private chat, knowledge base, self-assessment tools, and a list of locally available resources (see Fig 3).

**Fig 3 pone.0305729.g003:**
[figure not shown]
Summary of the Kampung Care app functions.

These components were proposed based on the Stress and Coping model [7] and our previous studies amongst local informal caregivers of PWD [25, 29, 42–45]. Based on the Stress and Coping model [7], different coping strategies may lead to different health outcomes by affecting the stress appraisal process. By adopting a variety of coping strategies frequently, caregivers may improve their threshold in appraising an event as stressful [25]. The ‘positive reflections’ function was adapted from benefit-finding interventions in the literature [46, 47], which involve writing about one’s positive thoughts and feelings about a stressful experience. The intervention aims to impart positive reframing as an adaptive coping skill which caregivers can routinely utilise as a coping resource to deal with the stress from caregiving. Positive reframing is known to be associated with enhanced psychological outcomes, including lower psychological distress in family caregivers [48]. Furthermore, since caregivers spend much of their time on caring, having a self-assessment tool for them to gauge their depressive and anxiety levels (i.e., common problems which dementia caregivers face) can be a fast and cost-effective way to monitor their mental health and alert them of the need to engage in self-care practices if they are experiencing distress.

Additionally, local caregivers of PWD from our previous research perceived educational content (i.e., videos and knowledge related to dementia, caregiving, and self-care) and social and emotional support (i.e., forum, support group, list of support resources and helplines) to be beneficial features of digital health interventions [29]. Drawing on these findings, we included the forum, private chat, resource list, and knowledge base as our app’s functions. The forum and private chat aim to provide an outlet for carers to share their thoughts and experiences and connect with other caregivers. Users can post content, reply to others, and receive notifications when new interactions occur. These interactions can provide natural triggers to maintain platform usage and may increase caregivers’ engagement with the app [49]. As caregivers also expressed often needing support in managing care for PWD, having the resource list function would direct them to relevant organisations and resources that could be useful. Finally, the knowledge base function was designed to provide curated information for the different stages of dementia and knowledge which can improve dementia literacy, coping, caregiving, and self-care [29].

### Intervention delivery

The intervention group will be required to use the Kampung Care app for one month. Caregivers will be asked to complete at least two positive reflection journal entries per week (i.e., one in the middle of the week and one at the end of the week) and encouraged to use other app features. However, the actual usage of the app is ultimately dependent on users based on their schedule and interests during the one month. Follow-up calls will be made by a study team member weekly to seek feedback, provide clarification and assistance if needed, and to remind and motivate caregivers to continue app usage. During the call in the second week of app usage, the Patient Health Questionnaire-9 (PHQ-9) will be used to assess users’ mental health to monitor their risk and provide self-help resources if necessary. In the meantime, caregivers in the control group will be placed on a waiting list for one month.

After the end of one month, the post-assessment will be conducted for both groups. Scores from the post-assessment will be compared with that for the baseline to determine the effectiveness of the app. Caregivers’ app usage will also be analysed to examine links between usage patterns and intervention effects. Participants in the control group will also be given access to the app after completing the post-assessment, but they can refuse if they do not want access.

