**Methods:**

A pilot two-armed randomised controlled trial will be conducted on 60 informal caregivers of PWD recruited via convenience and snowball sampling. Thirty participants will be assigned to the intervention group, while another 30 will be in a waiting-list control group. Questionnaires will be administered at baseline and one month after, with the primary outcome being the difference in the change of depressive symptoms among the two groups.

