**Statistical analysis:**

Primary analyses will follow the intention-to-treat principle and compare changes from baseline to the one-month follow-up time point relative to the control group. A repeated measures ANOVA will be conducted to examine differences between the groups over time.

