However, few of the apps presently available in the market have been developed specifically to address the needs of informal caregivers of PWD. A recent review by Castillo et al. [35] found only 16 apps which met their criteria for a focus on dementia care for informal caregivers of PWD, out of which only 3 were supported by some evidence in the literature. In another review, Brown et al. [36] identified only 5 out of 13 apps which had a focus on caregivers and all these apps had limited functions to meet the complex needs of caregivers of PWD. Lastly, a review by Rathnayake et al. [37] revealed a lack of rigorously designed studies with a clear theoretical framework and user-centered approach to app design. Findings from the above studies concurred that the apps reviewed were insufficient to address the multidimensional needs of caregivers of PWD and highlighted the need to develop more user-centered and evidence-based apps [35].

More importantly, none of the apps reviewed are based in Singapore. To the best of our knowledge, there is currently only one mobile app developed to support dementia caregivers in Singapore (i.e., CARA). Key features of the CARA app include (1) helping to locate and enable the safe return of missing PWD, (2) involving and notifying other family members by connecting with them through a connected care circle, (3) providing tailored discounts and privileges for members, and (4) access to a list of solution providers for various needs [38]. This highlights a clear gap in the development and empirical evaluation of mobile-based interventions with culturally sensitive resources for different stages of dementia in Singapore. This study will therefore evaluate the effectiveness of a multi-component mobile-based intervention comprising culturally relevant knowledge and resources aimed at improving mental health outcomes for informal caregivers of PWD in Singapore. We aim to examine differences in levels of depressive and anxiety symptoms, caregiver burden, mental well-being, caregiving self-efficacy, knowledge of dementia, positive aspects of caregiving, and coping strategies before and post-intervention, as well as between the intervention and control groups.

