### Data analysis

The primary analysis will compare the outcome measures between the intervention and control groups by following the intention-to-treat principle. Additionally, per-protocol analyses will also be conducted. All analyses will be done through SPSS V29 or SAS 9.4. A two-sided p-value below 0.05 will be deemed statistically significant. Results will be reported according to the Consolidated Standards of Reporting Trials (CONSORT) statement regarding eHealth [73]. The statistician in charge of the final analysis will be blinded to group allocation to minimise bias. Repeated measures ANOVA analyses will be done to evaluate differences between the two groups over time. In the case of multiple comparisons, Bonferroni adjustment of p-values will be applied to avoid over-interpretation of the results. Effect size (i.e., Cohen’s d) will also be calculated. For the qualitative data, the interviews will be audio-recorded and transcribed before the analysis. Data analysis will be conducted using thematic analysis as informed by Braun and Clarke [74], where key themes will be identified and refined. A codebook will also be developed to serve as a coding framework for coding of the transcripts. Data management and qualitative analysis will be done through NVivo V11.

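### One sentence judges the app's effectiveness by post-assessment against baseline, an uncontrolled comparison at odds with the between-group primary analysis stated elsewhere

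*Protocol article*

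**What the plan says.** The article describes the basis for judging the app in several places.

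- **Methods, Intervention delivery:** "Scores from the post-assessment will be compared with that for the baseline to determine the effectiveness of the app". The control group is not named in this sentence. The sentence before it reads "After the end of one month, the post-assessment will be conducted for both groups".
- **Background, Mobile-based interventions (closing statement of aims):** differences will be examined "before and post-intervention, as well as between the intervention and control groups".
- **Abstract, Methods:** one-month follow-up, "with the primary outcome being the difference in the change of depressive symptoms among the two groups".
- **Abstract, Statistical analysis:** the primary analyses follow intention to treat and "compare changes from baseline to the one-month follow-up time point relative to the control group".
- **Methods, Data analysis:** "The primary analysis will compare the outcome measures between the intervention and control groups by following the intention-to-treat principle", and "Repeated measures ANOVA analyses will be done to evaluate differences between the two groups over time".

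On usage, Intervention delivery adds that caregivers' "app usage will also be analysed to examine links between usage patterns and intervention effects". The same section leaves the amount of use to each participant's schedule and interests.

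**The concern.** A randomised trial with a waiting-list arm supports a claim of effectiveness through the difference between arms. A change from baseline within the app arm mixes any app effect with whatever would have happened anyway: regression to the mean, repeat assessment and natural fluctuation.

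This design is open to that. Study procedure admits only caregivers who score 4 or more on the 4-item Zarit Burden Interview. The 22-item version is a secondary outcome, so burden is directly exposed to regression to the mean. CES-D is exposed only as far as it correlates with the screening score.

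The risk lies in reporting. With 30 per arm, a null between-group result beside a significant improvement in the app arm could well occur. The sentence under Intervention delivery would then give a protocol-based reason to call the app effective.

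**Working it through.** **1. The sample-size figures.** Sample size states 25 per arm at 1:1, doubled to 100, then reduced to 60. The arithmetic holds: 25 × 2 = 50; 50 × 2 = 100; 30 × 2 = 60. The 25 comes from a cited recommendation and is not disputed here. The input used below is n = 30 per arm.

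**2. The statements side by side.**

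| Place | Comparator | Role |
|---|---|---|
| Abstract, Methods | Control arm (difference in change) | Primary outcome |
| Abstract, Statistical analysis | Control arm | Primary analysis, intention to treat |
| Data analysis | Control arm, repeated measures ANOVA | Primary analysis, intention to treat |
| Mobile-based interventions | Before/after, and separately the control arm | Aim |
| Intervention delivery | Baseline only | Said to determine effectiveness |

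The last row disagrees with the first three, and the aims do not settle the matter.

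**3. How often the before/after comparison misleads.** From the documents: n = 30 in the app arm and a two-sided 0.05 level (Data analysis). Assumed, because the documents give neither: a shared improvement of m SD in both arms with no app effect, and a baseline to follow-up correlation ρ of 0.5 to 0.7.

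- SD of the change, in units of the outcome SD: √(2(1 − ρ)). This is 1.000 at ρ = 0.5 and 0.775 at ρ = 0.7.
- Noncentrality of the paired t-test: m√30 / √(2(1 − ρ)), with 29 degrees of freedom and critical value 2.045.
- Example, m = 0.3: 0.3 × 5.477 / 1.000 = 1.643 at ρ = 0.5, and 0.3 × 5.477 / 0.775 = 2.121 at ρ = 0.7. The noncentral t gives 35.5% and 53.6%.

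| Shared drift m | Paired test, app arm, ρ = 0.5 | ρ = 0.7 |
|---|---|---|
| 0 | 5.0% | 5.0% |
| 0.1 SD | 8.3% | 10.5% |
| 0.2 SD | 18.5% | 27.7% |
| 0.3 SD | 35.5% | 53.6% |

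A simulation of 20,000 trials per setting agreed with these. In the same simulations the between-group test of change, which equals the group-by-time term when there are two time points, rejected in 4.8% to 5.2% of trials at every drift.

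**4. How easily the randomised test could be null.** For a true app effect of δ SD, the two-sample t-test on change scores has noncentrality δ√(30/2) / √(2(1 − ρ)), with 58 degrees of freedom. Power is about 12% to 17% at δ = 0.2 and 21% to 31% at δ = 0.3 (ρ 0.5 to 0.7). These effect sizes are illustrative; Sample size refers only to a small effect.

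**5. Precision of the between-group options.** Per participant, the variance is 2(1 − ρ) for the change score and 1 − ρ² after adjustment for baseline. The ratio is (1 − ρ²) / (2(1 − ρ)) = (1 + ρ)/2, which is 0.75 at ρ = 0.5 and 0.85 at ρ = 0.7. Baseline adjustment therefore removes 15% to 25% of the variance, using data already collected.

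**The case against.** The strongest reply is that the plan already fixes the randomised contrast. The Abstract and Data analysis both make it primary, under intention to treat. The disputed sentence sits in a procedural section, directly after one saying that both groups are assessed, and can be read as shorthand for computing change scores in both arms. No within-arm paired test is specified anywhere. This largely stands: the primary inference is not uncontrolled, and a reader who infers that the trial will be judged on before/after change alone goes beyond the text. It does not remove the conflict, because the sentence names only baseline and the aims set before/after differences beside between-group ones.

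A reader might also infer that effectiveness will be determined by links between usage and outcome. The document does not say so. Usage is introduced as an added analysis. It is non-randomised, because participants choose how much to use the app, but that bears on its interpretation only.

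The drift is assumed, and this objection stands in full. With no drift the paired test holds its 5%. For CES-D the route through selection is indirect. If the upper half of a normally distributed screening score were admitted (an assumption), the mean selected score is about 0.80 SD. Regression alone would then give 0.3 SD on CES-D only if the correlation with the screening score fell by 0.3 / 0.80 ≈ 0.38 within the month. Other sources of shared change could add to it, but the documents size none of them.

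Attention is not a good example of shared drift. The weekly calls are described as part of app use, while controls wait. Any effect of those calls would also enter the between-group difference, and this rewording does not address it.

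**Conclusion.** The point holds as an inconsistency in the stated basis for effectiveness. One sentence, supported by the wording of the aims, allows an uncontrolled comparison to decide whether the app works; the Abstract and Data analysis assign that decision to the randomised difference. Followed literally, the uncontrolled rule has a false-positive rate between 5% (no drift) and 36-54% (0.3 SD shared drift), against about 5% for the randomised test. These rates assume n = 30 with complete data, ρ of 0.5 to 0.7, and drift sizes that the documents do not supply, so they illustrate the exposure and do not forecast it. The primary analysis is not invalid, and no sample-size figure changes. The correction is still worth making, because it costs almost nothing and closes off an unsupported claim of success.

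**What to change.** Replace the sentence under Intervention delivery with wording such as: *Effectiveness will be judged only on the randomised between-group difference in CES-D at one month, by intention to treat, adjusted for baseline CES-D. Changes within each arm will be reported descriptively and will not be used as evidence of effectiveness.*

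If the sponsor prefers to keep the repeated measures ANOVA, name the group-by-time term as the test of effectiveness. That is valid, though less precise than baseline adjustment. Align the statement of aims with the same wording.

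Add that the usage analysis is exploratory because usage is self-selected. Its covariates, and those of the per-protocol analysis, may be left to the full plan.

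Cost: a sentence or two. The sponsor gives up the before/after claim. Sample size, assessments and conduct are unchanged.

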### Outcomes

Assessments to examine caregiver outcomes will be conducted at baseline and one month after baseline (post-assessment) for both the intervention and control groups. These will be conducted in English either online via videoconferencing or face-to-face at a location preferred by the participants.

The English version of the following questionnaires will be used in our study:

Centre for Epidemiological Studies-Depression (CES-D) ScaleGeneralized Anxiety Disorder– 7 item scaleZarit Burden InterviewRevised Scale for Caregiving Self-efficacyDementia Knowledge Assessment ScaleCoping Orientation to Problems ExperiencedPositive Aspects of Caregiving ScalePositive Mental Health instrument (short form)

The 20-item Centre for Epidemiological Study Scale (CES-D) will be used to measure the primary outcome–depressive symptoms amongst caregivers [50]. The instrument comprises 20 items, each rated on a 4-point Likert scale from 0 (*rarely or none of the time*) to 3 (*most or almost all the time*). The total score ranges from 0 to 60, with a score of 16 or higher indicating a risk for clinical depression [51]. The CES-D is a widely used scale which has been validated in Singapore [52] and was found to have an internal reliability of 0.91 when used in our previous study [25]. It also demonstrated good validity and reliability in detecting caregiver depression in another local study amongst caregivers of PWD [53]. Please see Table 1 for details on the secondary outcome measures.

**Table 1 pone.0305729.t001:** Measurement of secondary outcomes in the study.

Outcome	Questionnaire	Description
Anxiety	Generalized Anxiety Disorder– 7 item scale (GAD-7)	Each item of the Generalized Anxiety Disorder– 7 item scale (GAD-7) [54] is scored on a 4-point Likert scale from 0 (not at all) to 3 (nearly every day), with scores ranging from 0 to 21. A score of 10 or higher has been recommended as a cut-off point for identifying cases of GAD, while cut points of 5, 10, and 15 can be interpreted as mild, moderate, and severe levels of anxiety respectively [54]. The GAD-7 has been validated amongst the general population in Singapore [55] and used on a sample of local primary caregivers with a high internal consistency of 0.89 [56].
Caregiver burden	Zarit Burden Interview	The 22-item ZBI [57] assesses impairments on the caregiver’s health, psychological well-being, finances, and social life as a result of caregiving [58]. Each item is rated on a 5-point Likert scale from 0 (never) to 4 (nearly always present). A total score is obtained from summing up all items, with higher scores reflecting higher levels of burden. The instrument was previously validated in a local study in which it showed strong internal consistency, test-retest reliability, and construct validity when used on a sample of family caregivers [59]. In our prior research, the internal reliability of the ZBI was found to be 0.92 [25].
Caregivers’ level of self-efficacy	Revised Scale for Caregiving Self-efficacy (RSCSE)	The Revised Scale for Caregiving Self-efficacy (RSCSE) [60] comprises 15 items describing situations which caregivers may encounter regarding getting respite, responding to the care recipient’s memory and behavioral problems, and negative thoughts about their role as a caregiver. Caregivers will be asked to rate their level of confidence in overcoming these difficulties from 0 to 100, or not applicable if they feel that the item is not relevant to their current caregiving experience. The RSCSE is widely used globally and has been validated [61]. In our earlier study, the RSCSE’s 3-factor model was found to be robust and showed an acceptable fit amongst local caregivers [43].
Knowledge of dementia	Dementia Knowledge Assessment Scale (DKAS)	The 27-item Dementia Knowledge Assessment Scale (DKAS) [62] consists of statements on dementia, with some being factual, all with the response options: ‘*false*’, ‘*probably false*’, ‘*true*’, and ‘*probably true*’. For each item containing factual statements (e.g., ‘Exercise is generally beneficial for people experiencing dementia’), participants are given 1 or 2 points if they responded with ‘*probably true*’ or ‘*true*’ respectively, while all other responses are scored 0. For items with non-factual statements (e.g., ‘It is impossible to communicate with a person who has advanced dementia’), participants will be accorded 1 or 2 points if they responded with ‘*probable false*’ or ‘*false*’, respectively, while all other responses are accorded 0. The DKAS has been used in our previous studies amongst local caregivers of PWD [43, 63].
Coping strategy	brief Coping Orientation to Problems Experienced (COPE)	The brief Coping Orientation to Problems Experienced (COPE) [64] has 28 items measuring 14 different domains of coping, with two items for each domain. Caregivers are asked to rate how often they used each coping strategy to deal with stressful caregiving events during the past month on a 4-point Likert scale from 1 (‘*I haven’t been doing this at all’*) to 4 (‘*I’ve been doing this a lot’*) (Carver, 1997). This scale has been validated in a sample of caregivers of PWD, whereby it showed good internal consistency and construct validity [65]. When used in our earlier study, the brief COPE had an internal reliability of 0.88 [25]. It was also previously used amongst family caregivers of PWD in another local study [66].
Positive aspects of caregiving	Positive Aspects of Caregiving (PAC) Scale	Positive aspects of caregiving will be measured by the 9-item Positive Aspects of Caregiving (PAC) Scale [67], which is scored on a 5-point Likert scale ranging from 1 (*disagree a lot*) *to 5* (*agree a lot*). The overall PAC score ranges from 9 to 45, with a higher score reflecting a more positive perception of the caregiving experience. The reliability and validity of the PAC were established as acceptable amongst a sample of caregivers of older Singaporean adults with functional limitations [68], while other studies have also found similar results amongst caregivers of PWD [69, 70]. In our earlier study, the 2-factor structure of the PAC was found to be suitable when used amongst informal caregivers of PWD in Singapore [42].
Mental well-being	short Positive Mental Health (PMH) instrument	The short Positive Mental Health (PMH) instrument [71] is a short version of the original scale developed and validated in Singapore to measure the level of mental health in a general population [72]. It consists of 24 items, out of which 19 items assess six domains of mental health including general coping, emotional support, spirituality, interpersonal skills, personal growth and autonomy and global affect. Another five items are negatively worded filler items placed randomly to check for patterned responses. The ‘global affect’ subscale consists of three affect indicators which requires participants to rate from 1 (*never or very rarely*) to 5 (*very often or always*) how often they felt that over the past four weeks. For the rest of the subscales, participants are asked to indicate how much each item described them over the past 4 weeks on a scale from 1 (*not at all like me*) to 6 (*exactly like me*).

